## Abstract

**Background:**

Cognitive impairment is common in type 2 diabetes mellitus, and there is a strong association between type 2 diabetes and Alzheimer’s disease. However, we do not know which type 2 diabetes patients will dement or which biomarkers predict cognitive decline. Left ventricular hypertrophy (LVH) is potentially such a marker. LVH is highly prevalent in type 2 diabetes and is a strong, independent predictor of cardiovascular events. To date, no studies have investigated the association between LVH and cognitive decline in type 2 diabetes. The Diabetes and Dementia (D2) study is designed to establish whether patients with type 2 diabetes and LVH have increased rates of brain atrophy and cognitive decline.

**Methods:**

The D2 study is a single centre, observational, longitudinal case control study that will follow 168 adult patients aged >50 years with type 2 diabetes: 50% with LVH (case) and 50% without LVH (control). It will assess change in cardiovascular risk, brain imaging and neuropsychological testing between two time-points, baseline (0 months) and 24 months. The primary outcome is brain volume change at 24 months. The co-primary outcome is the presence of cognitive decline at 24 months. The secondary outcome is change in left ventricular mass associated with brain atrophy and cognitive decline at 24 months.

**Discussion:**

The D2 study will test the hypothesis that patients with type 2 diabetes and LVH will exhibit greater brain atrophy than those without LVH. An understanding of whether LVH contributes to cognitive decline, and in which patients, will allow us to identify patients at particular risk.

**Trial registration:**

Australian New Zealand Clinical Trials Registry (ACTRN12616000546459), date registered, 28/04/2016

**Electronic supplementary material:**

The online version of this article (doi:10.1186/s12902-017-0173-7) contains supplementary material, which is available to authorized users.

## Background

Type 2 diabetes mellitus is associated with an increased risk of dementia [1, 2] and more specifically, a two-fold increase in the risk of Alzheimer’s disease [3]. Many factors may contribute to this strong association, including increased stroke incidence, white matter microstructural changes, hyperinsulinaemia and metabolic syndrome, as well as the cross-association of mid-life obesity and type 2 diabetes [4]. A diagnosis of diabetes in midlife increases the risk of both vascular cognitive impairment and Alzheimer’s disease [5].

Magnetic resonance imaging (MRI) markers of structural brain aging such as reduced total brain volume, cortical thickness, hippocampal volume, and increasing white matter hyperintensity load, are correlated with performance on neuropsychological tests and are powerful predictors of dementia [6, 7]. A strong association between midlife vascular risk factors and structural brain aging has been demonstrated [8], although longitudinal brain volume changes have not been thoroughly examined in patients with type 2 diabetes. The PROSPER study findings suggested that elderly non-demented patients with type 2 diabetes had accelerated progression of brain atrophy compared to non-diabetic individuals and provided evidence for the hypothesis that diabetes exerts deleterious effects on neuronal integrity [9].

There is little evidence that intensive glycaemic management as reflected by lower HbA_1c_ levels in type 2 diabetes is associated with reduced dementia risk [10, 11] or cognitive decline [12]. The ACCORD-MIND study investigators [10] found no evidence that an intensive glycaemic treatment strategy targeting HbA_1c_ to <6% altered cognitive outcomes in patients with type 2 diabetes. However, the ACCORD study was halted due to higher mortality rates from cardiovascular events in the intensive arm [13]. Subsequent follow-up of the ACCORD-MIND participants found an association between poor cognitive function and the risk of severe hypoglycaemic events [14]. A further 80 months of follow-up in the ACCORDION MIND trial showed no long term benefits of intensive glycaemic control on cognition or brain MRI outcomes [15]. It therefore remains unclear if tight glycaemic control as reflected by lower HbA_1c_ levels lead to lower risk of dementia and better biomarkers are needed for the prediction of cognitive decline to stratify the risk of dementia in type 2 diabetes.

Patients with type 2 diabetes have associated hypertension [16], a high prevalence of previously unknown heart failure [17] and left ventricular dysfunction [17, 18]. Left ventricular hypertrophy (LVH) is also highly prevalent in patients with type 2 diabetes [18] and hypertension [19] and is an established independent predictor of adverse cardiovascular outcomes, including stroke [20] and heart failure [21]. Patients with type 2 diabetes and co-morbid hypertension have increased left ventricular mass, more concentric left ventricular geometry, lower myocardial function, that is independent of age, sex, body size, arterial blood pressure and atherosclerosis, compared to hypertensive individuals without type 2 diabetes [16]. Diabetes and hypertension predispose to the ischemic small vessel disease underlying lacunar infarction. Lacunar infarction can result in cognitive decline from selective damage to frontal-subcortical circuits subserving processing speed and executive function, and these deficits are often observed in type 2 diabetes [22].

There is a strong association between cardiac disease and impairment across many cognitive domains, particularly in tests of executive function [23]. Heart failure is strongly associated with cognitive impairment [24–26] and is an independent risk factor for the development of Alzheimer’s disease and cerebrovascular disease [16]. Carotid atherosclerosis is associated with cognitive impairment [27], measures of structural brain aging [8] and reductions in parietal gray matter [8]. LVH is associated with progressive cognitive decline, independent of blood pressure and large artery stiffness [28]. Left ventricular mass is associated with worse performance on tests of both visuospatial and verbal memory [29], and there is a nonlinear association between left ventricular ejection fraction (EF) and measures of accelerated structural and cognitive brain aging [30].

### The D2 (diabetes and dementia) study

The diabetes and dementia study (D2) study is an observational study in which we will intensively study the cardiovascular status of patients with type 2 diabetes and investigate if LVH predicts cognitive function, or if specific cardiac indices predict cognitive decline and brain atrophy. We will recruit participants with type 2 diabetes and integrate transthoracic echocardiography, carotid imaging, brain imaging with MRI, circulating and genetic biomarkers, and neuropsychology tools, to establish the relationship between type 2 diabetes, brain atrophy, and cognitive decline in a cohort of 168 individuals with and without LVH. At baseline, all participants will have structural neuroimaging with MRI to assess global brain volume, regional cortical thickness and hippocampal volume, a 12 lead electrocardiogram (ECG), an echocardiogram to assess the absence or presence of LVH, a carotid ultrasound to assess vascular disease, 24-h ambulatory blood pressure and ECG, cognitive assessment, and apolipoprotein E (*APOE*) gene risk assessment. All of the aforementioned assessment tools will be repeated at the 24-month follow up period.

## Methods

The D2 study has been approved by the Human Research Ethics Committee at Austin Health (HREC/15/Austin/490) and is registered at the Australian New Zealand Clinical Trials Registry (ACTRN12616000546459). Funding is provided through the National Health and Medical Research Council of Australia (APP1094974). Informed written consent is obtained from the participants prior to any data collection.

### D2 Study design

The D2 study is a single center, observational, longitudinal, case-control study. One hundred and sixty-eight adult patients, aged greater than 50 years with type 2 diabetes will be followed: 50% with LVH (case) and 50% without (control). Patients will be assessed at baseline (0 months) and will return for tests at the 24 month time-point. Based on recruitment in our other diabetes, cognitive and imaging trials, it is expected that 80–90 patients will be recruited annually for the first 2 years. Recruitment of new patients will be completed at the end of 2 years, allowing the next 2 years for follow-up.

### Study hypotheses

Patients with type 2 diabetes and LVH will exhibit greater brain atrophy as assessed by MRI structural changes than those without LVH.Brain atrophy as assessed by MRI structural changes will be associated with worse cognitive performance.Increased left ventricular mass with specific left ventricular geometric patterns will be associated with the most severe regional brain atrophy and cognitive decline.

### Study aims

To establish whether diabetic patients with LVH have increased rates of brain atrophy and cognitive decline.To establish whether the specific LV geometric measures are associated with these brain volume changes.

### Study outcome measures

Our primary endpoint is brain volume change at 2 years (hypothesis 1). Our co-primary outcome is the presence of cognitive decline at 2 years (hypothesis 2). We shall use advanced brain imaging to accurately measure brain volume and correlate this with cardiac echocardiography, carotid intima media thickness (CIMT), and 24 h blood pressure and ECG monitoring in 168 patients with type 2 diabetes, with longitudinal testing allowing measurement of change at 24 months. Concurrent neuropsychological testing will indicate whether the clinical profile of cognitive impairment and dementia aligns with measures of brain volume.

### Eligibility criteria

Inclusion criteria are as follows: (1) aged over 50 years; (2) no prior neurological or psychiatric disease, including stroke; (3) ability to give informed consent and participate in cognitive testing. The study exclusion criteria are as follows: (1) known prior stroke, transient ischemic attack or dementia; (2) significant medical co-morbidities precluding participation in cognitive testing, or making survival for 24 months unlikely; (3) normal exclusion criteria for MRI; e.g., implanted metal, severe claustrophobia; (4) severe diabetic nephropathy: estimated glomerular filtration rate (eGFR <30 mL/min/1.73 m^2^).

### Study assessments

The schedule of assessments is provided in Table 1. Testing will include the following: a pre-study screening questionnaire and MRI safety check to determine eligibility; demographic and medical history questionnaire; clinic measurement of height, weight, waist and hip; echocardiogram, ECG; CIMT; 24 h ambulatory blood pressure and ECG monitor; cognitive assessment; MRI scan; physical activity monitor; and a blood sample (to determine *APOE* genetic risk and analyses of genetic and plasma/serum biomarkers).

**Table 1 Tab1:** Schedule of assessments at baseline (0 months) and 24 months

Assessments	Brief description	Time-point (months)	
		0	24
Pre-study screening questionnaire (to determine study eligibility)	Study eligibility criteria	✓	
MRI safety check questionnaire	MRI eligibility	✓	✓
Demographic and medical history questionnaire	Questionnaire completed with the study investigator	✓	✓
Weight, height, waist and hip measurement	Clinical assessment	✓	✓
Transthoracic echocardiogram	Assess cardiac structure and function	✓	✓
Blood sample	Plasma electrolytes, glucose, HbA_1C_, lipids and urinary analyses. Blood collected for *APOE* genotyping and assessment of other genetic and circulating biomarkers.	✓	✓
Carotid intimal medial thickness	B-mode ultrasound to assess left and right internal carotid arteries and the degree of stenosis	✓	✓
24 h ambulatory blood pressure and ECG Holter	Simultaneous measurement of blood pressure and ECG	✓	✓
MRI scanning on a Siemens 3 T Skyra scanner using a 64 Channel receive only head coil.	• High resolution isotropic T1 3D MPRAGE (structural scan)	✓	✓
	• High resolution isotropic T2 FLAIR 3D		
	• High resolution isotropic T2 3D		
	• Susceptibility-weighted image (SWI) for iron deposition		
	• Diffusion-weighted imaging (DWI)		
	• GRE field mapping		
	• BOLD 7 min free run (resting state connectivity)		
Cognitive and mood evaluation	Validated tools for assessing mood, global cognitive ability, attention, visuospatial ability, executive function, language, memory, processing speed	✓	✓
Physical activity assessment	SenseWear Armband (BodyMedia FIT)	✓	✓

### Details of questionnaire and measurements

#### Pre-study screening and MRI safety check questionnaires

A short questionnaire will be used to ask questions related to the study eligibility, which will be key to identifying patients that may be unsuitable for MRI testing. Those identified as unsuitable will be informed at this stage and no further measurements will be conducted. Eligible participants will complete a detailed MRI safety questionnaire with the investigator to obtain more specific information about their history of surgical procedures to determine whether they have implants that might not be suitable for a 3 T MRI scan. Participants will be excluded if they cannot have a research 3 T MRI scan (e.g., because they have a metal implant that has not been cleared for safety in a 3 T MRI scanner).

#### Demographic and medical history questionnaire

A questionnaire and medical record review will be conducted at the time of the echocardiogram and blood collection. The following information will be collected: age, sex, duration of diabetes, smoking history, alcohol consumption, current drug therapy and dose, socioeconomic status family history of cardiovascular disease, medical history including general health and co-morbidities (cardiac disease, hypertension, dyslipidaemia, the presence of micro-vascular disease (nephropathy, retinopathy, neuropathy) and other macro-vascular complications (peripheral vascular disease). The questionnaire will be cross-checked by medical record review at Austin Health, and from their clinical and specialist reports if recruited outside of Austin Health.

#### Physical measurements

Participants’ height and weight (to determine body mass index (BMI) and body surface area) will be assessed. Weight will be measured to the nearest 0.1 kg on standing digital scales without shoes and light clothing. Height will be measured using a wall-mounted stadiometer to the nearest 0.1 cm. Waist and hip circumferences will be measured using a spring loaded tape. Waist circumference is measured at the mid-point between the lower costal margin and the iliac crest. Hip circumference is measured over the greater trochanters.

#### Transthoracic echocardiography (TTE)

TTE will be performed by a cardiologist using a commercially available portable ultrasound system (Vivid i, GE Healthcare). Standard parasternal and apical views will be used to assess left ventricular mass. Measurements are obtained according to the American Society of Echocardiography (ASE) recommendations [31]. M-mode echo will be used to measure cardiac dimensions and wall thickness. Ejection fraction will be calculated using the modified Simpson’s rule. Left ventricular mass will be indexed using the ASE corrected convention, by dividing left ventricular mass by height^2.7^. LVH will be defined as >49 g/m^2.7^ for males and >45 g/m^2.7^ for females. Relative wall thickness will be calculated, and left ventricular remodelling classified as normal, eccentric, or concentric remodelling and concentric LVH.

#### Blood collection and measurements

Fasting plasma electrolytes, glucose, HbA_1C_, lipids and urinary analyses will be obtained on all patients at baseline and at 24 months. The D2 study will collect additional plasma, serum and whole blood for genetic analyses. The exploration of novel circulating biomarkers and genetic determinations that lead to LVH and/or brain atrophy will be conducted within our laboratory. Whole blood will be collected and divided between lithium heparin and EDTA tubes for plasma and genetic samples and a plain tube for serum. Serum will be extracted and aliquoted for storage at -80 °C until assayed. For plasma, the sample tube will be stored on ice and centrifuged within 15 min to separate the plasma. The plasma will be aliquoted for storage at -80 °C until assayed. Whole blood will be collected in a potassium EDTA tube and immediately stored at -80 °C until DNA extraction. *APOE* genotyping will be performed in our laboratory. Genomic DNA will be extracted using the Qiagen DNA Maxi kit (Qiagen, Germany) and the *APOE* region of interest will be amplified with specific primers. The resulting DNA fragment will be sequenced in the forward and reverse direction on an ABI 3130-xl genetic analyser (Applied Biosystems, CA, USA). Participants will be informed of their *APOE* ε4 status by the Principle Investigator and those with *APOE* ε4 homozygosity will be offered counselling via the Neurogenetics Clinic at Austin Health.

#### Carotid Doppler ultrasound

CIMT measurements will be conducted in the Neurology diagnostics laboratory, Austin Health by a single technician. High-resolution B-mode ultrasound images will be obtained on both right and left internal carotid arteries. CIMT will be measured, and the degree of stenosis will also be classified into accepted clinical grades for incorporation into multivariate analyses: none, <50%, 50–69%, 70–79%, 80–89%, 90–99% and occluded (NASCET criteria) [32].

#### Ambulatory blood pressure and ECG monitoring

Each participant will have a combined Holter monitor simultaneously assessing ambulatory blood pressure and ECG data (CardXplore, Meditech, Hungary).

#### MRI acquisition and processing

Scans will be acquired for gray and white matter anatomical, structural and functional connectivity and iron estimation analyses. High resolution structural MRI of study subjects will be acquired using a 3 T Siemens Skyra MR scanner. The following sequences will be acquired: T1-weighted three-dimension (3D) magnetization-prepared rapid gradient-echo (MP-RAGE) for anatomical analyses; susceptibility-weighted image (SWI) for iron estimation and microhemorrhage imaging; fluid-attenuated inversion recovery (FLAIR) to assess chronic white matter ischemic changes and diffusion weighted imaging (DWI) to assess white matter structural integrity.

Regional cortical gray matter atrophy will be assessed using vertex-wise cortical thickness analysis. Cortical thickness will be mapped using the FreeSurfer software package for analysis of structural MRI data (http://surfer.nmr.mgh.harvard.edu/fswiki) [33]. The automated cortical and subcortical parcellation routines also provided with FreeSurfer will be used to investigate regional volume changes. We will use processing streams developed specifically by our group for longitudinal studies [34, 35]. Hippocampal volume changes will be assessed using manual hippocampal segmentation. Iron deposition and cerebral microbleeds will be assessed with susceptibility-weighted image analyses. The MRI protocol is provided in the Additional file 1.

#### Cognitive and mood assessment questionnaire and tests

Participants will complete a neuropsychological assessment. The assessment will include several paper-and-pencil and computerized cognitive tasks and mood questionnaires. Six cognitive domains will be examined, including (i) attention, (ii) visuospatial ability, (iii) executive function, (iv) language, (v) memory, and (vi) processing speed. The tasks used to measure each cognitive domain are listed in Table 2. This protocol has been modelled on that validated by the CANVAS study, a longitudinal study of patients after stroke [36]. All tasks are designed for serial testing and are less affected by practice effects. Performance on individual cognitive tests will be standardised using established norms and domain scores will be calculated by averaging the standardised scores from each contributing test (e.g., Trail Making Test as a measure of attention). Assessment of mood will be completed using the seven-item Generalized Anxiety Disorder (GAD-7) questionnaire and the nine-item Patient Health Questionnaire (PHQ-9). These questionnaires are based on criteria for the diagnosis of generalised anxiety and depression (Diagnostic and Statistical Manual-Fourth Edition: DSM-V) [37].

**Table 2 Tab2:** Tasks used to measure each cognitive domain

Cognitive domain	Cognitive task
Global Cognitive Ability	Montreal Cognitive Assessment [45]
	The Clinical Dementia Rating [46]
	National Adult Reading Task [47]
Attention	Trail-Making Test [48]
	Digit Span Task (WAIS-IV) [49]
	Identification Task (Computerised CogState battery) [50]
	One Back Task (Computerised) [50] CogState battery)
Visuospatial Ability	Rey Complex Figure Test (Copy) [51]
Executive Function	Clock Drawing Task – CLOX [52]
	Controlled Oral Word Association Test [53]
Language	30-item Boston Naming Test [54]
	Verbal Fluency Test [53]
Memory	Rey Auditory Verbal learning Task [55]
	Rey Complex Figure Test (Recall) [51]
Processing Speed	Detection Task (Computerized CogState battery) [50]
	Digit-Symbol Task (WAIS-IV) [49]

#### Physical activity monitoring

The SenseWear Pro2 Armband (HealthWear BodyMedia, Pittsburgh, PA, USA) is a portable device which enables monitoring of energy expenditure and activity. The device uses a two-axis accelerometer, a heat flux sensor, a galvanic skin response sensor, a skin temperature sensor, and a near-body ambient temperature sensor to capture data and will be worn by each participant on the upper arm for 7 days. The data will be converted into Metabolic Equivalents minutes (METs*minutes) and energy expenditure using an algorithm (Bodymedia, Sense Wear 6.1) [38]. The SenseWear monitor has been validated for measuring energy expenditure in diabetes against double-labeled water [39].

### Sample size

We aim to recruit 168 patients with type 2 diabetes. Patients will be divided based on the presence of LVH. Higher left ventricular mass and concentric geometric changes have been demonstrated in approximately 35–40% of patients with type 2 diabetes [16, 17]. Our data suggested more than 50% of participants will have LVH [18]. We calculated our sample size in order to include sufficient participant numbers for both the primary endpoint comparison (brain volume) and for the primary outcome measure (presence of cognitive impairment). The primary endpoint requires a direct comparison of two groups: type 2 diabetes patients with LVH and those without. We based our effect size on published brain volume and cortical thickness estimates performed on healthy controls, cerebrovascular disease patients and Alzheimer’s disease patients [40–42], and prior imaging of healthy controls and stroke patients performed by our group [43]. We use an average brain volume change of <0.5% per annum for controls, 1–2% for cerebrovascular disease, and 2–4% for dementia [44].

We used a modified retrospective case-control method. All participants have the exposure (type 2 diabetes), which will naturally halve by the additional risk factor (LVH, expected prevalence around 50%), but only some of them will develop the primary outcome (cognitive decline). We used an ANCOVA method to estimate sample size for four samples (cognitively impaired LVH, non-cognitively impaired LVH, cognitively impaired non-LVH, non-cognitively impaired non-LVH) with repeated measures, including a correlation score between baseline and follow-up. Using alpha = 0.05 (two-sided), power = 0.8 and an estimated correlation of 0.1, we estimated that 140 (i.e., 35 in each of 4 groups) participants will be required. Given we expect around 20% attrition due to death or non-participation (unable to participate in testing due to new pacemaker/implanted metal/other medical issue, lost to contact, no longer interested), we have estimated a total recruitment number of 168. This model has used the conservative estimates from these results and assumes the following: that 30% of patients will be cognitively impaired at 2 years; a 1% total annual brain volume change for patients with type 2 diabetes; that 30% of patients will exhibit specific left ventricular geometric changes; and a low correlation between baseline and follow-up measures.

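### The sample size is said to suffice for presence of cognitive impairment, but the only calculation uses impairment as a grouping factor, so power for decline by LVH status is not demonstrated

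*Protocol article*

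**What the plan says.** The Sample size section states that the number was chosen to be enough "for both the primary endpoint comparison (brain volume) and for the primary outcome measure (presence of cognitive impairment"). It then reports one calculation: "We used an ANCOVA method to estimate sample size for four samples (cognitively impaired LVH, non-cognitively impaired LVH, cognitively impaired non-LVH, non-cognitively impaired non-LVH"). The model allows for repeated measurement. The settings are "Using alpha = 0.05 (two-sided), power = 0.8 and an estimated correlation of 0.1", and the result is "we estimated that 140 (i.e., 35 in each of 4 groups) participants will be required". About 20% attrition takes this to 168 recruited. The listed assumptions include 30% of patients cognitively impaired at 2 years and a 1% annual brain volume change. LVH prevalence is expected to be around 50%.

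Cognitive decline is called an outcome in several places. The abstract and Study outcome measures make it co-primary: "Our co-primary outcome is the presence of cognitive decline at 2 years (hypothesis 2"). The Sample size section says of the participants, "but only some of them will develop the primary outcome (cognitive decline"). The first item under Study aims is "To establish whether diabetic patients with LVH have increased rates of brain atrophy and cognitive decline".

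Under Statistical analysis, Hypothesis 2 compares brain measures between impaired and normal participants at 2 years, and relates brain volume loss to impairment status by regression.

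**The concern.** Impairment appears in the power model as one of the two factors that form the groups. A design with 35 impaired and 35 unimpaired people in each LVH group fixes the impairment rate at 50% in both. It therefore contains no difference in rates between LVH and no LVH, and it cannot give power to detect one. The only cognitive input is an overall rate of 30%; no rate by LVH group, odds ratio or target difference enters the calculation as described.

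The absence of those inputs from a condensed article would not be a finding. The explicit statement of sufficiency is open to criticism, because the model offered in its support does not bear on the frequency of decline. A reader could take the 80% as covering the co-primary outcome, and could then give a non-significant cognitive result more weight than its precision allows.

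**Working it through.** **1. The plan's own figure.** 4 × 35 = 140. The 140 can be neither reproduced nor refuted, because the article gives no SD and no difference between the four groups. Solved backwards with the usual normal formula, d = (1.960 + 0.842) × √(2/n), 35 v 35 implies d = 0.67 and 70 v 70 implies d = 0.47. An ANCOVA with correlation 0.1 multiplies these by √(1 − 0.1²) = 0.995, which changes little. The 168 is 140 × 1.20; 168 less 20% leaves 134. Both 140 and 134 completers are used below.

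**2. Decline as a yes/no outcome, by LVH status.** Inputs from the article: 30% overall, two-sided alpha 0.05, power 0.8. Assumptions: an exact 1:1 LVH split among completers (the article expects around 50%), and rates placed symmetrically about 30%. The detectable difference Δ, with p₁ = 0.30 − Δ/2 and p₂ = 0.30 + Δ/2, solves

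Δ = 1.960 × √(2 × 0.30 × 0.70/n) + 0.842 × √([p₁(1 − p₁) + p₂(1 − p₂)]/n).

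- n = 70 per group: 1.960 × 0.0775 + 0.842 × 0.0753 = 0.152 + 0.063 = 0.215. This is 40.8% v 19.2%, odds ratio 2.9.
- n = 67 per group: 1.960 × 0.0792 + 0.842 × 0.0769 = 0.155 + 0.065 = 0.220. This is 41.0% v 19.0%, odds ratio 3.0.

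The article states no LVH effect on cognition, so a range is shown, by the same approximation:

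| Odds ratio | Rates | Power, 70 v 70 | Power, 67 v 67 |
|---|---|---|---|
| 1.5 | 34% v 26% | 19% | 19% |
| 2.0 | 37% v 23% | 46% | 44% |
| 2.5 | 39% v 21% | 68% | 66% |
| 3.0 | 41% v 19% | 83% | 81% |

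**3. Does the four-group 80% stand for the brain measure?** At 140 completers, half with LVH and 30% impaired in each half, the cells are 0.30 × 70 = 21 impaired and 0.70 × 70 = 49 unimpaired, twice. That is 21/49/21/49, against the stated 35 in each. Take the effect that gives 80% power at 35 v 35 (d = 0.68 by the t distribution, 0.67 by the normal).

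- 21 v 21 (impaired with LVH v impaired without): normal form, 0.67/√(2/21) = 2.17, so power = Φ(2.17 − 1.96) = 58%; by the t distribution, 57%.
- 21 v 49 (impaired v unimpaired within one LVH group): 0.67/√(1/21 + 1/49) = 2.57, so power = Φ(2.57 − 1.96) = 73%; by the t distribution, also 73%.

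Reaching 35 impaired in each LVH group at 30% would take 70/0.30, about 234 completers.

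**The case against.** The best defence is that the co-primary outcome is tied to hypothesis 2, and that hypothesis 2 is analysed by comparing brain measures between impaired and normal participants. A model of LVH by impairment with a brain measure as response contains that contrast. The article also describes a modified retrospective case-control method, in which the outcome does define the groups, and sufficient numbers may mean only enough impaired and unimpaired people to compare.

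Much of this stands. The calculation may be relevant to the hypothesis 2 contrast, and a reader should not infer that cognition was left out of the planning. But that contrast tests brain volume. It does not test whether decline occurs more often with LVH, which is the first aim and the natural sense of an outcome defined as the presence of decline. On this defence the cell sizes also matter, and 35 per cell does not fit 30% impairment.

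Three limits should be kept in view. The article does not name the ANCOVA response; brain volume is inferred from the effect-size sentences. The calculation for LVH v decline uses an assumed split of rates and a simple two-proportion test that the article does not assign to the co-primary outcome. No passage says that a null cognitive result would be taken as evidence of no association.

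**Conclusion.** The statement of sufficiency for the presence of cognitive impairment is not supported by the calculation offered for it. The model can at most serve comparisons of a continuous measure between groups.

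A reader might go further and infer that 140 is too few. The documents do not support that, because they state no LVH effect on cognition, and 140 completers do suffice for a difference of about 21.5 points or more. What can be said is that only a large effect is covered: an odds ratio of about 2.9 to 3.0, with less than even power at 2.0. This rests on the plan's 30% rate, a 1:1 LVH split and an unadjusted comparison.

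A reader might equally infer that the 80% is at least secure for brain volume. That is not supported either. The figure cannot be reproduced from the article, and its equal cells conflict with the article's own impairment rate.

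**What to change.** In the Sample size section:

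1. Remove the claim of sufficiency for the presence of cognitive impairment, or limit it to the comparison of brain measures between impaired and unimpaired participants.
2. State the detectable difference for cognitive decline, LVH v no LVH, with its assumptions: about 21.5 points at 140 completers (41% v 19%, odds ratio about 2.9) or 22 points at 134, and about 44 to 46% power at an odds ratio of 2.0.
3. State that a non-significant cognitive result will be interpreted through its confidence interval.
4. Do not restate 80% power for the four-group model as it stands. Recompute it with the expected cells of about 21/49/21/49, and give the SD and difference used.

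The cost is a few sentences and one recalculation. The only downside is a less favourable stated power. Enrolment and assessments need not change for this restatement.
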